**Vital parameters**	
	Respiratory rate [1/min]
	Blood pressure (syst./diast.) [mmHg]
	Heart rate [1/min]
	Oxygen saturation [%]
	Temperature [°C]
	Oxygen supply [l/min]
**Laboratory**	
	Leukocyte count [giga/l]
	CRP [mg/l]
	PCT [µg/l]
**Pulmonal Symptoms**	
	Newly appeared coughing? (yes/no)
	Dyspnea? (yes/no)
	Newly appeared purulent sputum? (yes/no)
	Increased respiratory secretion? (yes/no)
	Increased suctioning requirements? (yes/no)
	Bronchial breath sounds (free text)
	Aspiration (yes/no)
**Blood gas analysis**	
	paO_2_ [mmHg]
	paCO_2_ [mmHg]
**Escalation of therapy**	
	Admission to PACU or ICU (yes/no)
	NIV (yes/no)
	CPAP (yes/no)
	Intubation (yes/no)
	FiO_2_ [%]
	Antibiotics (free text)
	Dose of antibiotics (free text)
	Bronchodilating medication (free text)
	Dose of bronchodilating medication (free text)
**Thoracic imaging**	
	Chest radiography (free text)
	Computed tomography (free text)
**Mental status**	
	Overall score of the Mini-Cog test (3-word-recall-task and clock drawing test)

Table 3 contains parameters that are collected on postoperative visits on day 1,3 and 7; CPAP = continuous positive airway pressure, CRP = C-reactive protein, diast. = diastolic, FiO_2 _= fraction of inspired oxygen, ICU = intensive care unit, NIV = non-invasive ventilation, paCO_2 _= partial pressure of arterial carbon dioxide, paO_2 _= partial pressure of arterial oxygen, PACU = post-anaesthesia care unit, PCT = Procalcitonin, syst. = systolic.

Additionally, after hospital discharge, relevant pulmonary imaging, diagnoses or complications are extracted from the discharge letter.

Postoperative recovery and patient satisfaction as a secondary outcome parameter are going to be evaluated with the Quality of Recovery-9 (QoR-9) questionnaire (Table 4) on day 1,3, and 7 [22]. The score ranges from 0 to 18, with a higher score indicating a better subjective recovery.

**Table 4 pone.0329076.t004:** Quality of recovery-9 questionnaire.

QoR-9-Questions	Score
Had a feeling of general well-being.	Not at all = 0 points Some of the time = 1 point Most of the time = 2 points
Had support from others (especially doctors and nurses).	
Been able to understand instructions and advise. Not being confused.	
Been able to look after personal toilet and hygiene unaided.	
Been able to pass urine and having no trouble with bowel function.	
Been able to breathe easily.	
Experiencing headache, backache or muscle pains	Not at all = 2 points Some of the time = 1 point Most of the time = 0 points
Experiencing nausea, dry-retching or vomiting	
Experiencing severe pain or constant moderate pain	

The table was adapted from [22]; The article was published under the Creative Commons Attribution (CC BY 4.0) license (https://creativecommons.org/licenses/by/4.0/). QoR-9 = Quality of recovery-9.

Other secondary outcome parameters, hospital length of stay and in-hospital mortality, will be determined by a chart review after hospital discharge.

### Data management

A FileMaker™ database is used to record postoperative outcomes. Database constraints avoid duplicate entries and values outside the valid range of clinical routine data. The ARISCAT score will be determined pre-operatively with the help of a paper-based checklist. A detailed description of the score is provided in “Background and rationale”. The score has been validated in several European populations [15,23]. The primary endpoint, POPC, is defined according to the consensus definition of the StEP collaboration [1] and complemented by the definition of the EPCO task force [20]. The definition is described in detail in the chapter “Outcome”. As mental status is part of the StEP criteria, a brief cognitive screening test (Mini-Cog test) will be performed regularly during the post-operative visits. The sensitivity of this test is 0.76–0.99, and the specificity is 0.83–0.93 [24]. As a secondary endpoint, the Quality-of-Recovery 9 questionnaire will be applied to assess subjective recovery after surgery. The test is highly sensitive (0.92 ± 0.01) with a high negative predictive value (0.93 ± 0.01) in a German study collective [22]. The tests and the questionnaire are detailed in the chapter “Outcome”.

To promote participant retention, all outcome data will be assessed while the patient is still hospitalised. If a patient drops out, for example, because of withdrawal of consent or unexpected surgery rescheduling and therefore missed ultrasound, the study protocol will be stopped immediately, no further data will be collected, and already gathered data will be deleted. In case of patient discharge from the hospital before performing postoperative visits on days 3 and/or 7, the study protocol will continue, and the available data will be processed if the postoperative visit on day one is documented.

The data are collected and stored in different formats. The inclusion criteria as well as the ARISCAT score, are going to be collected paper-based in the pre-anaesthesia outpatient clinic. Lung ultrasound is performed with the SonoSite PX (Fujifilm SonoSite Inc., Bothell, Washington, USA). The imaging data is transferred to the hospital’s internal PACS and stored and processed in Digital Imaging and Communications in Medicine (DICOM) format within the Department of Radiology. Routinely collected perioperative data are stored in the hospital’s internal patient data management system (PDMS) in an Oracle8i database. The data is accessible via Structured Query language (SQL) and can be exported in csv format. Postoperative visits are conducted in the form of structured questionnaires using tablets. Data collection and processing are done with FileMaker Pro software (Claris, version 19.6.3.302). In the electronic data entry form for the postoperative visits, no user input is possible outside the valid value ranges for numerical data; dichotomous questions (yes/no) are documented with the help of radio buttons. The clock is drawn by the patient on the tablet and also stored in the database as a drawing. Together with the performance from the word-recall task, the score of the Mini-Cog test is calculated. Regarding the correct evaluation of the drawn clock, the score is cross-checked by a physician before it is finally transferred to the database. After patient discharge, discharge notes are searched for relevant diagnoses and complications. The total volume of data collected will be merged into a comprehensive FileMaker database. Data storage occurs pseudonymized and de-identified.

No laboratory evaluations or biological specimens outside the clinical routine will be obtained or stored as part of this study. For the detection of postoperative pulmonary complications, diagnostic tests and relevant results performed by the respective departments will be collected during a chart review and directly transferred to the pseudonymized data collection.

Any documents with identifiable information will be collected in paper-based form and stored in a locked cabinet at the study centre, where only authorised personnel will have access to them. This includes original informed consent, a checklist with eligibility criteria, the ARISCAT score, and the patient identification list. The documents will be kept there until completion of the study. The identification list will be stored separately, and only authorised study personnel will have access to it. After completion of the study, all paper records will be stored in a central archive for at least ten years according to the clinic’s specifications and legal requirements. Information collected during the postoperative visits will be saved without any identifiable information on password-protected study tablets. After transferring the data to a hospital-internal computer, they are deleted from the tablets.

Pseudonymised data received from PDMS, chart review, and postoperative visits will be securely stored in the hospital’s internal server infrastructure according to GDPR requirements. Imaging data is exclusively stored within the clinic’s radiology information system.

### Statistical methods

The primary objective of the PEPPERMINT study is to develop and evaluate prediction models for postoperative pulmonary complications (POPC) using prospectively collected clinical and imaging data. Model development and validation will be conducted in accordance with the TRIPOD (Transparent Reporting of a Multivariable Prediction Model for Individual Prognosis or Diagnosis) guidelines. The statistical analysis plan is provided in S3 File.

### Overview of modelling approaches

Three predictive modelling strategies will be pursued. First, an imaging model will be created using deep learning techniques applied to lung ultrasound images. This model will be developed in Python using the PyTorch framework. Transfer learning will be employed, utilizing pretrained convolutional neural network (CNN) architectures such as ResNet or DenseNet. These models will be fine-tuned on the study-specific dataset. We will also assess the performance of medical foundation models and contrastive learning-based pretraining to optimize feature extraction from the ultrasound images.

Second, a clinical model will be developed using only structured patient data. This model will be trained using frameworks like H2O AutoML within R/RStudio as well as built-in R functions, which allows for the systematic evaluation and tuning of various machine learning algorithms, including gradient boosting machines, random forests, and neural networks.

Third, a combined model will integrate both clinical and imaging data. Various fusion strategies will be explored, including early and late fusion, to determine the most effective method for combining heterogeneous data types. The final architecture for this combined model will be selected based on performance observed in a hold-out test dataset.

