### Three predictive models will be developed

First, a model based on deep learning using lung ultrasound images, second, a model based solely on clinical variables using common frameworks like automated machine learning (AutoML), and finally, a combined model integrating both clinical and imaging features.

The dataset will be split using stratified, patient-wise sampling into non-overlapping training and hold-out test sets. Internal model performance will be assessed using k-fold cross-validation within the training set, and final evaluation will be conducted on the independent test set. Full details of the modelling and validation procedures are provided in the statistical methods.

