### Model training and evaluation

The primary model development will be based on a dataset of 512 patients. Within this cohort, we will implement stratified k-fold cross-validation (typically 5- or 10-fold, depending on the final class distribution) where possible to assess model robustness and mitigate overfitting. Image-based deep learning models require extensive computational resources, therefore, cross-validation will be applied more selectively. We will therefore use a fixed training/validation/test split for imaging data, ensuring non-overlapping patient groups. Early model experiments will be conducted using internal validation on the training data with hold-out validation to optimize architecture and hyperparameters. Final model evaluation will be performed on an independent hold-out test set.

This hold-out test set will be compiled prospectively during the course of the study after model development, using newly enrolled patients not included in the training dataset. This temporal separation will ensure unbiased performance evaluation of the final model.

Model performance will be evaluated on the independent hold-out test set using several complementary performance metrics. These will include the area under the receiver operating characteristic curve (AUROC), the area under the precision-recall curve (AUPRC), overall accuracy, sensitivity, specificity, F1-score, as well as positive and negative predictive values. Calibration will be assessed using appropriate measures, such as the Brier score, Hosmer-Lemeshaw-Test and calibration curves. Clinical decision-making utility can additionally be evaluated using decision curve analysis (DCA).

Importantly, our models are designed to output individualized risk probabilities, not dichotomous predictions. As such, the selection of a cut-off point for potential clinical decision-making will be a post-modelling step, and risk thresholds for high-risk patient classification will not be predefined. Instead, various thresholding strategies will be explored post hoc, including Youden’s index (for balanced sensitivity and specificity), cut-offs optimized for specific clinical priorities (e.g., maximizing sensitivity), and thresholds guided by DCA.

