### Missing values and data imputation

With regard to imaging data, only complete data sets will be accepted for analysis.

Missing values in the clinical dataset will initially be handled using the default preprocessing pipeline in the case that H2O AutoML is used. This pipeline applies median or mean imputation for numerical variables and mode imputation for categorical variables (https://docs.h2o.ai/h2o/latest-stable/h2o-docs/data-munging/imputing-data.html). In addition to this standard approach, we will evaluate alternative imputation strategies, particularly for approximately normally distributed numerical variables. These include, e.g., k-nearest neighbors (kNN) imputation, which leverages similarities across observations in the multivariate feature space and multiple imputation using chained equations (MICE), which incorporates multivariable relationships and reflects the uncertainty associated with imputed values.

Given the prospective nature of the study, we anticipate that most missing data will not be missing at random (NMAR), but rather occur systematically, for instance, due to early patient discharge or an inability to perform assessments as a result of clinical deterioration. In such cases, the absence of data may itself be informative with respect to the patient’s risk for postoperative complications. Therefore, in addition to the imputation techniques mentioned above, we will explore modelling strategies that explicitly account for informative missingness. These include the incorporation of missingness indicators (binary flags denoting whether a variable was observed or missing) and sensitivity analyses to assess the robustness of model predictions under different assumptions about the missing data mechanism.

The final approach to handling missing data will be selected based on a combination of model performance, diagnostic checks, and clinical plausibility.

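### The rule for choosing the combined model's architecture uses a hold-out test dataset, which conflicts with keeping the hold-out test set independent for final evaluation; if followed, the combined model's reported performance is biased upward

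*Protocol article*

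**What the plan says.** Under Overview of modelling approaches, the combined model is to be built by trying several ways of joining the two data types: "Various fusion strategies will be explored, including early and late fusion, to determine the most effective method for combining heterogeneous data types". The choice among them follows this rule: "The final architecture for this combined model will be selected based on performance observed in a hold-out test dataset".

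The section Three predictive models will be developed describes one patient-wise split into training and hold-out test sets and gives them different jobs: "Internal model performance will be assessed using k-fold cross-validation within the training set, and final evaluation will be conducted on the independent test set".

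Model training and evaluation agrees on the role of the test set: "Final model evaluation will be performed on an independent hold-out test set", and "Model performance will be evaluated on the independent hold-out test set using several complementary performance metrics". It adds that this set will be made up of newly enrolled patients once model development is over, and that the separation in time guarantees an unbiased evaluation. It also places architecture tuning elsewhere: "Early model experiments will be conducted using internal validation on the training data with hold-out validation to optimize architecture and hyperparameters". For imaging data it mentions a fixed split with a training, a validation and a test part.

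**The concern.** When several candidates are compared on one set of patients and the best is kept, part of the winner's lead is chance. If its AUROC is then reported from those same patients, the estimate is too high on average. ARISCAT is a fixed score and gets no such lift, so the comparison tilts towards the model. The same holds for the step from the imaging model to the combined model, because the article states no test-set selection rule for the imaging model. That step is the secondary objective (Objectives). The combined model is also the product that the Introduction, Discussion and Strengths sections describe. What is at stake is whether its headline performance can be called unbiased, as Model training and evaluation does.

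**Working it through.** **Step 1. The statements side by side.**

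| Section | Where architecture is chosen | Role of the hold-out test set |
|---|---|---|
| Three predictive models will be developed | not stated | final evaluation |
| Overview of modelling approaches | on a hold-out test dataset (combined model) | selection |
| Model training and evaluation | validation inside the training data (early experiments) | final evaluation, on new patients, after development |
| Adverse events and harms (modelling text placed there) | not stated; development on the whole dataset with cross-validation | validation on a temporally independent set |

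Choosing a fusion architecture is part of model development. A set assembled only after development cannot also be the set on which that choice is made. The second row therefore conflicts with the third, and with the first as well if the same set is meant. No section names a further untouched set reserved for the combined model after selection.

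**Step 2. The plan's own figure.** The 512 patients under Sample size (AUROC 0.93 against 0.83, significance level 0.05, power 80%) do not bear on this point. The figure has no unique reproduction, because that section gives neither POPC prevalence nor the correlation between the curves. Nothing below depends on it.

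**Step 3. Size of the optimism if the rule is followed.**

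Inputs from the article: ARISCAT AUROC 0.83 (Sample size); POPC frequency 43%, 111 of 259 (preliminary study, Addressing overfitting and class imbalance).

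Assumptions, because the article gives no figure:
- test set of 77, 102 or 154 patients (15%, 20% or 30% of 512);
- K = 3, 5 or 10 candidates;
- correlation ρ between candidates of 0.5 to 0.9;
- every candidate's true AUROC equal to ARISCAT's 0.83.

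Standard error of one AUROC (Hanley and McNeil), with n1 events, n0 non-events, a = A/(2−A) and b = 2A²/(1+A):

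var(A) = [A(1−A) + (n1−1)(a−A²) + (n0−1)(b−A²)] / (n1·n0)

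At A = 0.83, a = 0.7094, b = 0.7529 and A² = 0.6889. With 43% events:
- n = 77: SE = 0.0494
- n = 102: SE = 0.0428
- n = 154: SE = 0.0348

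The expected excess of the best of K equally good, equally correlated candidates is about SE × √(1−ρ) × m(K). Here m(K) is the mean of the largest of K independent standard normal values: m(3) = 0.846, m(10) = 1.539.
- Mild end (n = 154, ρ = 0.9, K = 3): 0.0348 × 0.316 × 0.846 = 0.009
- Strong end (n = 77, ρ = 0.5, K = 10): 0.0494 × 0.707 × 1.539 = 0.054

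A simulation with binormal scores, keeping the candidate with the best test-set AUROC and comparing it with ARISCAT by a paired DeLong test (two-sided 0.05, counting wins for the model), gave:

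| K | Optimism in AUROC | False wins over ARISCAT |
|---|---|---|
| no selection | 0 | about 2–3% (nominal 2.5%) |
| 3 | 0.009 to 0.031 | 3.5 to 6.6% |
| 5 | 0.013 to 0.040 | 3.9 to 8.2% |
| 10 | 0.016 to 0.052 | 5.5 to 13% |

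The hand formula and the simulation agree closely at both ends. The planned difference is 0.93 − 0.83 = 0.10, so the optimism is roughly one tenth to one half of it.

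**The case against.** The strongest reply is that the selection rule speaks of a hold-out test dataset without saying which. It may mean the test part of the fixed imaging split, with the later prospective patients left untouched. Model training and evaluation supports this: it tunes architecture by validation on training data and assembles the evaluation set afterwards. Under that reading there is no bias in the final figures. The reply stands in part. A reader might infer that the final test set is certain to be contaminated, and the article does not establish that. But it does not state the benign reading either, and both sections that assign the hold-out test set a role make it the final evaluation set. The conflict remains on any reading.

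A reader might also infer that the primary claim against ARISCAT is biased. The article does not support this. The rule covers only the combined model, whereas the primary objective concerns the imaging model.

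Third, one might add that cut-offs and the imputation method are chosen on test patients. The article says "various thresholding strategies will be explored post hoc" and "The final approach to handling missing data will be selected based on a combination of model performance, diagnostic checks, and clinical plausibility", but names no data set for either choice, and the analysis plan in S3 File, which is not at hand, may settle it. These are openings for the same reuse, not stated errors.

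Finally, the size may be small. Only two fusion types are named, so ten candidates is a generous assumption. With 512 test patients the simulated optimism falls to 0.006 to 0.019, across true AUROCs of 0.83 to 0.93. The false-win figures apply only if the model has no true advantage. All of this is correct and limits the claim about size. It does not remove the contradiction.

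**Conclusion.** The point holds as a contradiction within the protocol article with a definite consequence if the selection rule is applied as written: the combined model's test-set AUROC, its apparent gain over the imaging model and its comparison with ARISCAT would be too favourable, and the evaluation could not be called unbiased. Under the assumptions above the optimism is about 0.01 to 0.05 in AUROC, and false wins over ARISCAT rise from about 2.5% to about 3.5 to 13%. The optimism does not vanish for a good model: with true AUROC 0.93 and 102 test patients it is still 0.016 to 0.027 for 5 to 10 candidates at correlation 0.5 to 0.8. The direction is certain. The size is not, because the article gives neither the number of candidates, nor their correlation, nor the number of test patients; the false-win rate also depends on how strongly the candidates correlate with ARISCAT. The point does not extend to the primary imaging comparison, nor to cut-offs and imputation as stated faults.

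**What to change.** Replace the selection sentence under Overview of modelling approaches with wording such as: *The final fusion architecture will be selected by cross-validation or on the validation split within the development data; the model is then locked and applied once to the prospectively compiled hold-out test set.* Bring Three predictive models will be developed and Model training and evaluation into line, so that one hold-out test set is named, with its source and its single use. If the test part of the fixed imaging split is a different set from the prospective one, say so and give each its own name.

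As a precaution, also fix the imputation method in the development data, together with any cut-off used for test-set sensitivity, specificity, PPV, NPV and F1.

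The cost is a change of wording. The validation data already planned are enough, so nested cross-validation for every choice is not required, and no extra patients are needed. The reported AUROC of the combined model may come out slightly lower. The change must be made before the test set is used, because selection on it cannot be undone afterwards; Trial status lists 150 patients included out of the 512 planned.
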